**Dietary processes**	
Amounts of key promoted foods consumed by pregnant women	
Intra-household allocation, as PW’s share {PW/(PW + senior male)} of nutrients in term of Mean probability of micronutrient adequacy, iron intake, and energy adequacy	
Weight gain in pregnancy from enrolment to 30 ± 2 weeks (kg)	
**Side effects**	
Constipation^1^	
Indigestion/heart burn^1^	
Vomiting^1^	

^1^These process indicators will be reported in the main trial paper whereas others may be reported in one or more separate process evaluation publications rather than in the trial paper

For the purposes of tracking any potential harms, we track side effects from taking IFA tablets including vomiting, constipation and indigestion or heart burn and report them to the DMC.

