#### Insufficient dietary intake

Micronutrient deficiencies in Nepalese women are largely attributable to inadequate diets. Although dietary inadequacies have been reported for many micronutrients [29–32], attaining adequate dietary iron intake is particularly challenging [29, 30, 33, 34], especially in pregnancy due to the increased requirements. In the plains of Nepal, the probability of dietary iron adequacy is only 20% and intake of animal-source foods are low [30]. Dietary intake is also inequitable, with gender-based discrimination and food restrictions preventing PW from accessing high status, relatively expensive micronutrient-rich foods [31, 35–38]. Low awareness of dietary needs in pregnancy [36], food taboos [38] and household power hierarchies [36] may also prevent households from providing micronutrient-rich foods to PW even when they are available. Women may also ‘eat down’ or eat less than they did before pregnancy for numerous reasons, including fear of obstructed labour if the baby is large [39], religious fasting, misconceptions about the stomach/intestines ‘squashing’ the baby, morning sickness (especially in early pregnancy), discomfort or indigestion from eating large meals [40], food aversion and proscriptions such as avoiding foods believed to heat the body [41, 42].

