### Criteria for discontinuing or modifying allocated interventions {11b}

We do not expect that the tailored counselling or PLA women’s groups to have any negative effects upon trial participants, but some women may experience side effects from consuming IFA or from deworming. Side effects commonly experienced from IFA include constipation and indigestion [1, 89], but these tend not to be serious. Recent studies have also indicated that iron supplementation may increase susceptibility to infections but that this is more common in children than adults [90]. Interviewers will collect data on side effects of IFA and on morbidity of women during the 30 ± 2-week interviews and NAs will ask women about side effects and advise how to mitigate them during counselling sessions and at women’s groups. In exceptional cases, if the higher IFA dose is not being tolerated, the NA may advise the woman to reduce intake from two to one tablet per day. All women who are feeling unwell at the time of interaction with the NA or data collector are advised to seek care at their nearby health facility or at a higher care centre where needed.

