### Procedure for unblinding if needed {17b}

The design is open label with only outcome assessors being blinded so unblinding will not occur. Interim reports for the Data Monitoring Committee (DMC) and Trial Steering Committee (TSC) regarding recruitment, follow-up and baseline characteristics are unblinded. Interim safety reports (morbidity and side effects) for the DMC will be initially blinded but can be unblinded on request of the DMC if differences are observed.

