### Interim analyses {21b}

No interim analyses of intervention effectiveness are planned. Interim reports for the Data Monitoring Committee (DMC) and Trial Steering Committee (TSC) regarding recruitment, follow-up and baseline characteristics will be prepared and interim safety reports (morbidity and side effects) for the DMC.

We do not specify a formal stopping rule since the interventions under test are simply adapting WHO and government policies for IFA supplementation that are already in use. So, whilst women may consume more IFA tablets as a result of the intervention, there is no new drug being tested. The risk during the finger prick test for Hemocue testing to know the haemoglobin status is low. We also do not intend to consider modification or early stopping of the trial on the basis of interim evidence of intervention effectiveness (or lack of effectiveness). Nevertheless, the DMC is presented with harms data (adverse events and levels of morbidity) disaggregated by study arm at each meeting and could recommend to the Trial Steering Committee modification or termination of the trial.

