### Adverse event reporting and harms {22}

Surveillance questionnaires and questions posed during counselling sessions will assess side effects of taking IFA which we expect will mostly be mild symptoms including dark stool, nausea, bloating, abdominal discomfort, heartburn, loss of appetite, metallic taste and constipation. The most serious problems that could arise may be a severe allergic reaction to IFA (though this is very rare) or participants contracting COVID-19 after interacting with a trial team member. In addition, our primary outcome questionnaire will record recalled symptoms of illness including pre-eclampsia, vaginal bleeding, dysentery, gestational diabetes and malaria, though none of these are expected to be associated with our intervention.

Although we do not expect any adverse effects of attending a PLA group, of being visited for counselling or interviews/measurements, we will establish a complaints procedure and ensure that trial participants and their families know who to call or where to visit to register a complaint. Contact details are provided in the participation information sheet, and participants will be reminded of the complaints procedure at each visit.

If any unanticipated effects (including maternal deaths or COVID-19 cases associated with trial participation) are noted by the NAs, interviewers or dietary data collectors, they will inform field coordinators / managers who will telephone and/or visit the home of the respondent to ascertain the extent and nature of the problem and complete an adverse events form. Investigators will then classify each event as a minor adverse reaction (MAR), severe adverse reaction (SAR), severe adverse event (SAE) or suspected unexpected serious adverse reaction (SUSAR). These will be presented to PIs and to the Data Monitoring Committee where appropriate. In the case of illness, all participants are referred to the appropriate referral centre depending on the severity of their condition.

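### Three tracked harms are defined as side effects of IFA, with an extra source in the intervention arm, so comparing them by arm is liable to count background symptoms more often there

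*Protocol article*

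**What the plan says.** Table 2 (Outcomes {12}) lists constipation, indigestion or heartburn, and vomiting under a side-effects heading, and its footnote commits them to the main trial paper. The sentence on harms below the table reads: "we track side effects from taking IFA tablets including vomiting, constipation and indigestion or heart burn and report them to the DMC".

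The data come from two places. Section {11b} says "Interviewers will collect data on side effects of IFA and on morbidity of women during the 30 ± 2-week interviews", which covers both arms, and adds that "NAs will ask women about side effects and advise how to mitigate them during counselling sessions". Section {22} puts the two together: "Surveillance questionnaires and questions posed during counselling sessions will assess side effects of taking IFA". Counselling sessions belong to the home visits, so they exist only in the intervention arm.

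On use of the data, section {17b} lists morbidity and side effects as the content of interim safety reports to the DMC. These are blinded at first but "can be unblinded on request of the DMC if differences are observed". Section {21b} says that "the DMC is presented with harms data (adverse events and levels of morbidity) disaggregated by study arm at each meeting". Section {20a} says that Table 2 process indicators are analysed in a similar way to the outcomes.

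**The concern.** A woman who takes no IFA cannot have a side effect of IFA. When a harm is defined by attribution to the tablet, both IFA use and the woman's belief about cause decide whether a symptom counts. Both can differ by arm. The Sample size {14} section expects lower IFA intake in control clusters, and Interim analyses {21b} accepts that intervention women may take more tablets. The nutrition assistants and the women's groups also discuss IFA side effects with intervention women.

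The same complaints arise without iron. The Background (Insufficient dietary intake) gives "morning sickness (especially in early pregnancy), discomfort or indigestion from eating large meals" among the reasons why pregnant women eat less. An identical episode of heartburn could therefore be counted in an intervention woman and missed in a control woman who is off IFA or does not link it to the tablets.

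At stake is the side-effect comparison in the main paper, and what the DMC sees when it decides whether to ask for unblinding. The primary outcome is not affected.

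**Working it through.** The article gives no figure for this comparison, so there is none to reproduce. The check sets the passages side by side and then illustrates the size.

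**1. Is the definition tied to IFA?** Yes. The sentence below Table 2, {11b} and {22} all speak of side effects of IFA, and Objectives {7} speaks of side effects of iron therapy.

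**2. Do the symptoms occur without IFA?** The Background says so for sickness and indigestion. It does not mention constipation.

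**3. Does IFA use differ by arm after randomisation?** The plan expects it to ({14}, {21b}).

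**4. Is enquiry equal?** Both arms have the 30 ± 2-week interview. Intervention women are also asked at up to two home visits, which makes up to three occasions against one. This matters only if counselling reports enter the comparison. The article names them as a source and does not exclude them.

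**5. Size, with no true effect of the package on the symptoms.** Let *p* be the risk of a background symptom that would be blamed on IFA, and *u* the share of women on IFA. If risk is proportional to being on IFA:

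- counted risk = *u* × *p*
- spurious risk ratio = *u*(intervention) / *u*(control)
- spurious difference = (*u*(intervention) − *u*(control)) × *p*

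Inputs: *u*(control) = 0.91, the 2016 national share given some IFA (Background, IFA supplementation and antenatal care). *u*(intervention) = 1 is an assumption.

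- Risk ratio = 1/0.91 = 1.10.
- The difference depends on *p*, which the article does not give. Assume a weekly background rate of 1%, 3% or 6% over an equal nine weeks in both arms, with *p* = 1 − exp(−rate × 9):

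| Weekly rate (assumed) | Intervention | Control (× 0.91) | Difference |
|---|---|---|---|
| 1% | 8.6% | 7.8% | 0.8 points |
| 3% | 23.7% | 21.5% | 2.1 points |
| 6% | 41.7% | 38.0% | 3.8 points |

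- With control exposure assumed at 75% or 67% of the intervention arm's, the ratio would be 1/0.75 = 1.33 or 1/0.67 = 1.49. Nothing in the article fixes these exposures.

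**6. Under the proposed definition.** If every woman is asked whatever her IFA use, *u* drops out. The counted risk is *p* in both arms, and the ratio under no true effect is 1.00.

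**7. A related inconsistency.** Control exposure depends partly on when routine IFA starts. The Background gives 14 weeks' gestation and Strategies to improve adherence {11c} gives 20 weeks. The two must be reconciled.

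**The case against.** The strongest reply is that the bias is inferred from a phrase. Table 2 lists bare symptoms. The questionnaire is not shown, and an article may leave item wording to it. General morbidity ({11b}, {22}) and pregnancy symptoms (Enrolment of trial participants) are also collected without reference to IFA, and {21b} describes the DMC's by-arm data as adverse events and morbidity. Tolerability of iron is itself a stated process measure. Most control women will take some IFA, and {6b} notes that menstrual monitoring in both arms may bring it forward.

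Much of this stands, and it rules out several stronger readings:

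- **A counting window that opens with the first tablet.** A reader might infer one, but no window, recall period, denominator or filter to IFA takers is written. Both arms are interviewed at the same target gestation.
- **Harms recorded only through attribution to IFA.** This is untrue of harms overall. It describes how these three are defined. Whether the general items cover them is not stated, since the named illnesses do not include them and the list is open.
- **A comparison that is certainly biased, with a high false-positive rate.** Extra symptoms caused by extra IFA are a real effect. High rejection rates would need assumed low control exposure, and no test on side effects is expressly specified.
- **The same flaw in the adverse-event classes.** The MAR/SAR/SAE/SUSAR scheme in {22} is for unanticipated effects noted by staff, which is a separate data stream.
- **An automatic trigger for unblinding.** It is at the DMC's request, and there is no formal stopping rule.

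The reply does not remove the attribution wording in three operative places, or the naming of an intervention-only source beside the common one.

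**Conclusion.** The point holds as a liability to differential ascertainment, not as a demonstrated bias. As worded, the three harms depend on IFA use and on attribution, both of which arise after randomisation, and one named source exists in one arm only. The expected direction is over-counting of background symptoms in the intervention arm.

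The size is unknown. The only share of IFA users in the article gives a spurious risk ratio of about 1.10. That assumes universal use in the intervention arm, 91% in control, risk proportional to being on IFA, and equal readiness to blame the tablets. The 91% is a national figure for receiving any IFA, so it is only a rough guide to exposure in the control clusters.

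Restricting the comparison to IFA takers would not repair it, because that compares groups selected after randomisation.

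**What to change.** In {11b}, the sentence below Table 2 and {22}, state that:

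- at the 30 ± 2-week interview the same interviewers ask every woman in both arms whether she had vomiting, constipation, or indigestion or heartburn;
- the questions cover one fixed recall period, apply whatever her IFA use, and come before any question on cause;
- the proportions are compared among all women as randomised, in DMC reports and in the main paper;
- attribution to IFA, and side effects recorded at counselling sessions, are reported descriptively only, outside the by-arm comparison.

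The recall period should have a fixed length, because the article allows outcome collection up to delivery if the pandemic disrupts visits. Separately, reconcile the two statements of when routine IFA starts.

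The cost is small: wording in three places, a check of the questionnaire items and a sentence in the analysis plan, with no new visits or staff. The article's Trial status section puts the start of recruitment in the future. One downside is that symptoms unrelated to IFA add noise and make the comparison less specific to iron. The change also does not remove any tendency of unblinded, counselled women to report more symptoms.

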### Participant timeline {13}

Formative work ran from May 2019 to February 2020 but trial roll-out was delayed because of the Novel SARS-CoV-2 Corona Virus (COVID-19) pandemic which began to affect Nepal in March 2020, just as trial enrolment was due to begin. Since census data is now out of date, several months of formal menstrual monitoring consent-taking and updating the census with new women or households is required before enrolment can begin. The trial timeline from when we are able to start the trial, showing the schedule of enrolment, interventions and assessments (as per the SPIRIT figure guidelines), is provided in Fig. 5. Data collectors will enrol women for one run-in and six full-trial months and follow-up every woman until the last enrolled woman reaches 30 ± 2 weeks. The ‘full-trial’ phase will last for 14 months and only women recruited after the run-in month will be included in the final analysis.

**Fig. 5 Fig5:**
[figure not shown]
Schedule of enrolment, interventions, and assessments (SPIRIT Figure)

### Sample size {14}

Our trial includes 54 clusters with 6 months of enrolment. We assume 2.52 pregnancies will be detected per month per 1000 population, based on the rate observed in LBWSAT, which used a similar pregnancy detection mechanism. For women to be recruited, their pregnancy must be detected at < 20 weeks’ gestation. In LBWSAT, 55% of the pregnancies detected were < 20 weeks’ gestation at enrolment. So, for our sample size calculations, we assumed a best-case scenario of 50% and a worst case of 33% detected pregnancies < 20 weeks. We assume 20% loss to follow-up from enrolment to measurement of the primary outcome at 30 ± 2 weeks gestation, including losses due to miscarriage or termination and women migrating to their parental homes during pregnancy. Therefore, for the best- and worst-case enrolment scenarios, we expect an average of 15.6 and 10.4 primary outcome measures achieved per cluster respectively, giving us a sample size of 421 and 281 PW in each arm (or 842 and 562 women in the full trial).

We used Hb data provided by the Suaahara nutrition programme 2017 annual survey [91] from the neighbouring plains district of Rupandehi, to inform our sample size estimates. These data, which were sampled on the basis of old VDC wards that are the same as our cluster definition, provided a standard deviation (SD) of Hb of 1.2 and an intracluster correlation coefficient (ICC) of 0.09.

A Cochrane review showed a mean difference of Hb 0.888 g/L (95% CI 0.696 to 1.080) between PW supplemented with iron versus women without supplements [43]. Since in our control clusters we expect lower intakes of IFA and iron-rich food than in intervention clusters, we consider a 0.4 g/dL difference in Hb at 30 ± 2 weeks of gestation between trial arms plausible. We also consider this effect size to be of clinical importance.

Our power calculations are based on a difference of 0.4 g/dL Hb between arms in the primary outcome, an ICC of 0.09 and SD of Hb of 1.2 (or 1.25) g/dL and a coefficient of variation (CV) in cluster size of 0.27, based on CAPPT census data. We assume two-sided testing at the 5% significance level. In the best-case scenario of 50% of pregnancies being < 20 weeks’ gestation, the design provides 88% power assuming an SD of 1.2 and 86% power with an SD of 1.25. Full details of the power available in the different scenarios and details of the number of cases to be enrolled in the full trial (before loss to follow-up) are given in Table 3. Expected pregnancies and population per cluster used in power calculations are provided in Supplementary Annex 7.

**Table 3 Tab3:** Power calculations based on different standard deviations and proportion of pregnancies detected < 20 weeks

% of pregnancies < 20 weeks^1^	No of clusters per arm	Average number of Hb outcomes per cluster	ICC (rho)	CV cluster size	Detectable difference in Hb	Power with SD of 1.2	Power with SD of 1.25
50%	27	15.6	0.09	0.27	0.4	88.3%	85.7%
33%	27	10.4	0.09	0.27	0.4	82.1%	79.0%

^1^enrolment cut-off is ≤ 19 weeks 6 days gestation

### Recruitment {15}

Strategies to achieve adequate participant enrolment to reach the target sample size include monitoring menstruation of all consenting non-pregnant eligible women in the cluster and a free urine pregnancy test (UPT) after one or more missed menstrual period so that pregnancies are enrolled before 20 weeks. We provide FCHVs a monthly travel allowance plus an additional incentive on the basis of pregnancies detected. We conservatively accounted for only 33 to 50% of pregnancies being detected < 20 weeks, 20% loss to follow-up, and will allow 1 month for trial run-in to iron out problems at the start. To increase the response rate in later pregnancy, we provide an incentive to trial participants (NPR 1000) at the 30 ± 2-week interview.

## Assignment of interventions: allocation

### Sequence generation {16a}

To randomly allocate clusters to two arms, we used covariate-based constrained randomisation, drawing upon census data to characterise clusters to enable a similar population composition between study arms. The trial statistician (AC) randomly generated 5000 potential allocations based on computer-generated random permutation, from which 4206 were rejected on the basis of any of the following thresholds for the difference in cluster mean between arms:
Difference in % Muslim more than 5Difference in % hills ethnicity more than 2Difference in number of eligible women more than 17Difference in travel time to health centre on foot more than 3.5 minDifference in travel time to health centre by vehicle more than 2 min

These thresholds were set at approximately 0.25 of the SD in cluster summary value across the 54 clusters for each covariate and were considered adequate for good balance. We did not restrict the randomisation more strictly because of concerns this might impact on the type 1 error, for example as pairs of clusters tended to be allocated to the same arm. The remaining 794 candidate allocations were found unique and 12 were selected at random. A final list of 24 potential allocations was prepared, in which each of the 12 allocations was applied in the 2 possible ways (0/1 is either control/intervention or intervention/control) to ensure exactly equal chance of each cluster being allocated to control or intervention.

### Concealment mechanism {16b}

To ensure the randomisation process was observed to be fair, we held a meeting with municipality and health system leaders in March 2021 where we introduced the trial and invited a leader to randomly pick out the chosen randomisation option from a box of ping-pong balls labelled with the randomisation number. The allocation to arms was revealed to stakeholders and trial team members at the same moment in this public forum by a community stakeholder opening a sealed envelope with the chosen randomisation sequence and reading it out to the group.

### Implementation {16c}

The potential cluster allocation sequences were generated by the trial statistician (AC), and the final selection at the meeting (as described above) was made in advance of any recruitment of participants. Participants will be enrolled by field staff on the basis of meeting eligibility criteria and their cluster of residence determines allocation.

## Assignment of interventions: blinding

### Who will be blinded {17a}

After assignment of clusters to study arms, blinding of trial staff and participants is impossible, since the interventions are implemented at a cluster level and are publicised amongst community representatives, health workers and policymakers, to increase intervention uptake. Data collectors who collect primary outcome haemoglobin measurements and other secondary outcomes will know the study arm of the participant at the time of data collection, but since the Hb reading is a digital read out from a Hemocue analyser, the risk of bias in collection of the primary outcome is low.

